## Abstract

**Background:**

Stroke is a group of diseases with neurological deficits caused by cerebrovascular lesions. Despite standard treatment, a large number of patients are left with significant upper extremity motor dysfunction. Therefore, improving upper limb motor function and promoting neurological recovery in stroke patients has become a core challenge in the field of neurorehabilitation.

**Methods and analysis:**

This study will be designed as a randomized, sham controlled clinical trial. Thirty-six patients with upper limb motor dysfunction after stroke will be included, and their Fugl-Meyer Upper Extremity Motor Function Rating Scale (FMA-UE) score will be ≤ 26 points. Subjects will be randomly assigned to the following three groups (*n* = 12/group): HF-rTMS: Treated with high-frequency (5 Hz) repetitive transcranial magnetic stimulation (rTMS) on the dorsal premotor cortex (PMd) on the contralesional side. Low-frequency group (LF-rTMS): Treated with low-frequency (1 Hz) rTMS on the primary motor cortex (M1) on the contralesional side. Sham control group: The stimulation target and parameter settings will be the same as those of the high-frequency group, but the coil will be placed perpendicular to the scalp plane. The intervention regimen will be rTMS treatment once daily, five times a week for 3 weeks. Outcome measures: Main outcome measures: Upper limb motor function, assessed by FMA-UE. Secondary outcomes: Barthel Index (BI), National Institutes of Health Stroke Scale (NIHSS). Exploratory indicators: fMRI data and motor evoked potential (MEP) parameters. All assessment data will be collected before and after the intervention.

**Communication and ethics:**

This study has been reviewed and approved by the Basic and Clinical Research Ethics Committee of Sichuan Provincial People’s Hospital (Lun Shen (Yan) No. 353–1 of 2025). The results of this research will be disseminated through the network of professionals and the general public, and peer-reviewed scientific papers will be published and presented at relevant conferences.

**Registration:**

This trial has been registered with the Chinese Clinical Trials Registry with registration number ChiCTR2500105502.

## Introduction

Stroke is a group of neurological dysfunction diseases caused by cerebrovascular lesions. Clinically, such patients are often accompanied by varying degrees of motor and sensory dysfunction. The disease is characterized by high morbidity, disability and mortality rates, and has become the leading cause of disability in China (1, 2). Studies have shown that even with early intervention and standardized treatment, 55–75% of stroke patients still have persistent upper limb motor dysfunction (3, 4). Such dysfunction has a long recovery cycle and poor curative effect, which is strongly correlated with the significant decline in activities of daily living (ADL) and the deterioration of quality of life after stroke (5–8), and brings heavy economic burden to the social medical system and family care. Epidemiological data show that about 50% of stroke survivors have severe upper limb motor dysfunction (9), which is characterized by the near loss of voluntary mobility of shoulder, elbow, wrist and hand joints, resulting in the inability to complete basic daily activities (10). Current treatment strategies for patients with severe dysfunction are limited and clinical response rates are not ideal. Therefore, it is still a scientific problem that needs to be broken through in the field of neurorehabilitation to explore effective intervention methods to improve severe upper limb motor dysfunction after stroke, promote the mechanism of neural remodeling, and maximize the recovery of patients’ ADL ability.

Repetitive Transcranial Magnetic Stimulation (rTMS), as a non-invasive neuromodulation technology, evokes induced currents in cortical neurons through time-varying magnetic fields based on the principle of electromagnetic induction, and then regulates target cortical excitability, neuroplasticity and neurometabolism-electrophysiological activities (11–13). Current clinical practice mainly employs two modes: high-frequency stimulation (> 1 Hz) enhances cortical excitability and low-frequency stimulation (≤ 1 Hz) inhibits cortical excitability (14). This technique has been widely used in the treatment of neuropsychiatric diseases such as Parkinson’s disease and depression, and has been confirmed to have significant clinical efficacy (15). In the field of stroke rehabilitation, mainstream intervention strategies follow the Interhemispheric Competition Model (16): high-frequency rTMS targets the primary motor cortex of the ipsilesional side (iM1) to enhance the excitability of the damaged hemisphere; low-frequency rTMS acts on the primary motor cortex of the contralesional side (cM1) to inhibit the hyperexcitability of the contralesional hemisphere. However, this model has limitations in patients with severe injury to the Corticospinal Tract (CST) (17–19). With significant loss of corticospinal connectivity on the affected side (20), conventional interventions based on the competitive model are difficult to induce effective functional recovery. In response to this problem, Di Pino et al. proposed the Bimodal Balance-Recovery Model (BBRM) (12), pointing out that when the integrity of CST on the ipsilesional side is severely damaged, the contralateral hemisphere compensatory mechanism may dominate the reconstruction of motor function. Exciting the contralateral cortex may be a better strategy. In addition, most repetitive transcranial magnetic stimulation (rTMS) experiments in stroke rehabilitation studies focus only on the M1 area. When the corticospinal tract (CST) is severely damaged, the pattern of brain reorganization may not only be related to the M1 region, but also involve secondary motor areas closely connected to M1. Existing studies have shown that the dorsal premotor cortex (PMd) is involved in the coordination and control of complex hand movements (21). Therefore, for patients with severe brain injury, the contralateral dorsal premotor cortex (cPMd) could be a more valuable alternative, given its higher survival probability and richer descending projection network (22).

In this randomized sham-controlled trial, functional Magnetic Resonance Imaging (fMRI) and Motor Evoked Potentials (MEP) were integrated in addition to the standardized upper limb motor function scale. The main objectives of this experiment are as follows: 1. To analyze the dynamic changes in brain network structure and functional connectivity after intervention. 2. To establish a correlation model between clinical functional improvement and neuroimaging/electrophysiological indicators. 3. Explain the neural remodeling mechanism of upper limb functional rehabilitation after stroke (23). Core scientific hypothesis: High-frequency rTMS targeting the contralateral dorsal Premotor Cortex (cPMd) can significantly promote the recovery of upper limb motor function in patients with severe stroke. This study will provide new evidence for the mechanism of rTMS regulating neural compensation after stroke, and promote the development of precise neurorehabilitation strategies.

## Methods

### Objectives

To explore whether the high-frequency rTMS scheme of cPMd can more effectively compensate for the instability of its therapeutic effect than the low-frequency repetitive transcranial magnetism (rTMS) scheme of cM1.

### Study design

This study is a randomized sham-controlled clinical trial divided into high-frequency, low-frequency and sham-control groups. This study will be carried out in the Department of Rehabilitation Medicine of Sichuan Provincial People’s Hospital. Potential patients will be provided with detailed project information as well as full interpretation of informed consent. In order to improve patient compliance and reduce dropout rates, we will fully communicate before the trial to ensure that patients fully understand the significance of the study and voluntarily sign an informed consent form to participate. Subjects who met the inclusion criteria will be randomly assigned to three groups at a 1: 1: 1 ratio (n = 12 per group): high-frequency intervention group (5 Hz rTMS in the contralateral PMd region); Low-frequency intervention group (1 Hz rTMS in the ipsilesional M1 region); Sham stimulation control group (parameters were the same as high frequency group, coils were placed vertically). This study protocol has been reviewed and approved by the Basic and Clinical Research Ethics Committee of Sichuan Provincial People’s Hospital (Lun Shen (Yan) No. 353–1 of 2025), and has been registered with the China Clinical Trial Registry (ChiCTR) (registration number ChiCTR2500105502). Figure 1 shows the experimental flow chart.

**Figure 1 fig1:**
[figure not shown]
Flow chart showing the study design. cM1, contralesional primary motor cortex; rTMS, repetitive transcranial magnetic stimulation; cPMd, contralesional dorsal premotor cortex; MEP, Motor Evoked Potentials.

### Participants and eligibility

#### Enrollment criteria

The following are the inclusion criteria: (1) meet the diagnostic criteria for stroke: according to the “Guidelines for the Diagnosis and Treatment of Cerebral Hemorrhage in China (2019)” or “Guidelines for the Diagnosis and Treatment of Acute Ischemic Stroke in China (2018),” the diagnosis is confirmed by head CT/MRI imaging; (2)characteristics of stroke attack: initial unilateral onset, or no sequelae of neurological deficit left by previous stroke attacks; (3) vital signs and consciousness state: Vital signs are stable for ≥ 24 h, Glasgow Coma Scale (GCS) score = 15 points;(4) age range: 18–75 years old; (5) upper limb motor deficit: baseline Fugl-Meyer Upper Limb Motor Function Rating Scale (FMA-UE) score ≤ 26 points (suggesting severe motor impairment) (18); (6) informed consent: Voluntary written informed consent; (7) Recruiting patients within 1 week to 6 months after stroke.

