#### Randomization and blinding

Based on the sample size calculation, this study will enroll a total of 36 eligible subjects. Patients will be numbered sequentially according to their enrollment time and randomly assigned to one of three groups in a 1:1:1 ratio using a random number table. The study personnel responsible will number the patients and perform the randomization. Each numbered treatment protocol will be placed individually into an opaque, sealed envelope. Therapists will open the envelopes in numerical order and administer the treatment according to the corresponding protocol. The group codes will not be revealed until all analyses are completed. The sham stimulation group will use a mock device identical in appearance to the real equipment to replicate the look and acoustic noise of the active coil. The TMS operators will not be involved in trial design, assessment, or data analysis. Except for discussing discomfort or adverse effects, they will be prohibited from communicating any trial details with the subjects. All clinical assessors, behavioral therapists, data analysts, and other research staff will remain blinded to the group assignments (25).

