## Discussion and conclusions

In recent years, many studies have confirmed that repetitive transcranial magnetism (rTMS) can effectively improve the motor function of stroke hemiplegic patients (36, 37). But there are also studies that have found negative results, and some patients even have functional degeneration (38, 39). These evidences suggest that standardized rTMS protocols based on the theory of bilateral primary motor cortex (M1) IHI imbalance have limitations in clinical practice (40). Patients with chronic stroke accompanied by severe motor impairments have widespread damage to the neural pathways in the affected hemisphere, resulting in the M1 region being unable to effectively promote motor function recovery, ultimately leading to the failure of repetitive transcranial magnetic stimulation (rTMS) therapy (41). Therefore, this study will focus on cPMd therapies based on the latest “bimodal equilibrium-recovery model” (12).

This study is the first to systematically evaluate the efficacy of high-frequency rTMS targeting the anterior dorsal motor cortex (cPMd) on the unaffected side on severe upper limb motor dysfunction after stroke. Based on the theoretical framework of the Bimodal Balance-Recovery Model (BBRM), we propose the following core mechanism hypothesis: when the corticospinal tract on the affected side is severely damaged, high-frequency stimulation of the unaffected side cPMd can significantly improve the recovery of motor function by enhancing transhemispheric compensatory nerve remodeling. This effect may involve: (1) reversal of inhibitory regulatory imbalance: regulation of pathological interhemispheric inhibition; (2) activation of compensatory pathways: promote synaptic plasticity of the unaffected hemisphere-spinal anterior horn network. The results of this study will provide key evidence for precision neurological rehabilitation: in the future, rTMS treatment plans need to stratify patients according to the time window of injury, lesion localization and CST integrity, so as to achieve individualized intervention. In addition, the cPMd high-frequency stimulation paradigm is expected to be extended to the neuromodulation of multi-domain dysfunctions such as aphasia and swallowing disorders after stroke.

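### The Discussion's hypothesis is about severe corticospinal tract damage, but entry, allocation and the between-group model make no use of tract status, so the trial as written cannot confirm it

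*Protocol article*

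**What the plan says.** **Hypotheses.** The protocol article gives two, with different populations.
- Introduction, core hypothesis: high-frequency cPMd stimulation "can significantly promote the recovery of upper limb motor function in patients with severe stroke". There is no tract condition.
- Discussion and conclusions, hypothesis on the mechanism: "when the corticospinal tract on the affected side is severely damaged, high-frequency stimulation of the unaffected side cPMd can significantly improve the recovery". This is conditional on tract damage. The Introduction's account of the bimodal balance-recovery model carries the same condition.

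**Rationale.** The Discussion explains the failure of M1 treatment from chronic patients: "Patients with chronic stroke accompanied by severe motor impairments have widespread damage to the neural pathways in the affected hemisphere".

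**Entry.** Under Enrollment criteria, motor severity is set by one item, a baseline FMA-UE "score ≤ 26 points (suggesting severe motor impairment"), and the time window by "Recruiting patients within 1 week to 6 months after stroke". No MEP, DTI or other tract criterion appears there or under Exclusion criteria.

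**Allocation.** Under Randomization and blinding, patients are "randomly assigned to one of three groups in a 1:1:1 ratio using a random number table". No stratification factor is named.

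**Measurement and analysis.** Affected-side MEP is recorded before and after treatment (Scale and electrophysiological assessment). FA and the FA asymmetry index are obtained by DTI as measures of tract integrity (fMRI scan). Under Data processing and analysis, treatment group is the only between-group factor and time the only within-group factor. Imaging is linked to the clinical scales only by correlation tests.

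**Stratification.** Looking to the future, the Discussion says that "rTMS treatment plans need to stratify patients according to the time window of injury, lesion localization and CST integrity".

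**The concern.** FMA-UE scores behaviour. The protocol treats tract integrity as a separate quantity, since it measures it separately by MEP and DTI. A patient with a low FMA-UE score and a responsive affected-side tract is therefore eligible, although the mechanism hypothesis is not about that patient. On the usual reading of chronic stroke as more than 6 months (an assumption, as the article does not define the term), no chronic patient can enter.

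Two things are at stake. First, an overall result describes a mix of tract states, so it cannot be attributed to the severely damaged group without an analysis by tract status, and none is stated. Second, with 12 per arm, tract status and time since stroke can fall unevenly across arms by chance, and neither the allocation nor the model limits or absorbs this. Who is enrolled and how patients are allocated are protocol matters that the article does state, so this is not detail left to an analysis plan.

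**Working it through.** **1. The populations side by side**

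| | Time since stroke | Motor severity | Tract status |
|---|---|---|---|
| Core hypothesis (Introduction) | not stated | severe | not stated |
| Mechanism hypothesis (Discussion) | not stated; rationale argues from chronic | severe | severely damaged |
| Patients enrolled | 1 week to 6 months | FMA-UE ≤ 26 | any |

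The enrolled patients match the first row and not the second.

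**2. Plan figures used**

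The plan has 9 per group before dropout, 20% dropout and 12 per group (Sample size calculations). The dropout step reproduces: 9 / (1 − 0.20) = 11.25, rounded up to 12. The 9 itself does not follow from the stated ANOVA inputs, which give 2 or 3 per group. That is a separate matter, and nothing here depends on it.

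**3. How many patients the mechanism hypothesis concerns**

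The article gives no prevalence of severe tract damage at FMA-UE ≤ 26, so a range is assumed. Expected number per arm = 12 × prevalence; after dropout, that number × 0.80.

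| Assumed prevalence | Per arm | After 20% dropout |
|---|---|---|
| 25% | 3 | 2.4 |
| 50% | 6 | 4.8 |
| 75% | 9 | 7.2 |

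**4. Chance imbalance without stratification**

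Let K of 36 patients have the factor, with a fixed 12/12/12 split. The counts a, b, c per arm (a + b + c = K) have probability C(12,a) × C(12,b) × C(12,c) / C(36,K). Summing over all combinations gives:

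| K of 36 | Two given arms differ by ≥ 3 | by ≥ 4 | Some pair differs by ≥ 3 | by ≥ 4 |
|---|---|---|---|---|
| 9 or 27 | 0.246 | 0.101 | 0.429 | 0.225 |
| 12 or 24 | 0.286 | 0.133 | 0.490 | 0.283 |
| 18 | 0.314 | 0.158 | 0.530 | 0.325 |

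These probabilities are two-sided. An imbalance in one named direction is half as likely: 0.158 / 2 = 0.079 for 4 or more between two given arms at K = 18.

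**5. What an imbalance does to a contrast**

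Shift = (imbalance / 12) × D, where D is the difference in mean FMA-UE gain between patients with and without the factor. For an imbalance of 4 the shift is D/3. The article gives no D.
- An even mix of two groups that differ by D has an SD of at least D/2. If the planning SDs (0.9, 1.4 and 1.3) describe such mixes, then D is at most 2 × 1.4 = 2.8 and the shift at most 2.8 / 3 = 0.93 points.
- The planned differences are 11.4 − 2.8 = 8.6 (high-frequency versus sham), 11.4 − 4.7 = 6.7 (high- versus low-frequency) and 4.7 − 2.8 = 1.9 (low-frequency versus sham). To cancel them, an imbalance of 4 would need D of 25.8, 20.1 and 5.7 points.

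**6. What stratifying achieves**

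With blocks of 3 or 6 in each MEP stratum, only the last, incomplete block can be unbalanced. The arms then differ by at most 2 patients in each stratum as randomised, whatever the prevalence.

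**The case against.** The case for leaving the design alone has real force.

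- **The core hypothesis is met.** The Introduction's hypothesis and the sample-size objective concern severe stroke, and FMA-UE ≤ 26 selects severe impairment. A reader might infer that the trial cannot support its claim at all. The documents do not support that: the failure is confined to the tract-conditional statement in the Discussion.
- **Tract status is measured.** It would be wrong to say that it is unknown. The fair criticism is that MEP and DTI serve neither entry, nor allocation, nor a stated comparison of treatment effects by tract status.
- **The remark on stratification is about the future.** It concerns later treatment plans that these results should inform. A reader might take it as the protocol contradicting its own allocation; it is not. It does show that the authors regard time window and tract integrity as relevant to response.
- **Chance imbalance is not bias.** It is part of the sampling error of a randomised comparison, and simple allocation of 36 patients is defensible. This stands.
- **The effect on the main contrasts is easily exaggerated.** If the two patient types were assumed to differ by 6 to 10 points in gain, an imbalance of 4 would shift a contrast by 2.0 to 3.3 points, more than the 1.9 planned for low-frequency versus sham. That assumption has no source in the article and implies an SD of at least 3 to 5, against the stated 0.9 to 1.4. The high-frequency contrasts, which the hypothesis is about, are 6.7 and 8.6.
- **Chronic stroke appears in the rationale only.** The article does not claim to treat it. The limitations paragraph also concedes that the small single-centre sample restricts generality, though it does not mention tract status.

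What remains is the mismatch between the mechanism hypothesis and the patients enrolled, with tract measures collected and left out of the design.

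**Conclusion.** The concern holds in a limited form. The trial can test whether high-frequency cPMd stimulation helps patients with FMA-UE ≤ 26 between 1 week and 6 months after stroke. As written, it cannot confirm that the effect occurs in severe corticospinal damage, and it gives no direct evidence on chronic stroke.

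At an assumed 50% prevalence, about 6 per arm are the patients the mechanism hypothesis is about, and 4 to 5 after dropout. Imbalances of 4 or more arise in about 16% of trials for two given arms and 32% for any pair. At 25% or 75% these fall to about 10% and 23%. The consequence is lost precision and an unsupported attribution, not a biased comparison.

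The result rests on the assumed prevalence, on treating severe damage as a yes/no factor with absent affected-side MEP as its stand-in, and on a fixed 12/12/12 split. The size of any shift in FMA-UE cannot be fixed from the article. This is a worthwhile and inexpensive improvement, not a flaw that invalidates the trial.

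**What to change.** 1. **Randomization and blinding:** stratify allocation by baseline affected-side MEP, present or absent, with small blocks of varying size (for example 3 and 6) and a separate set of sealed envelopes for each stratum.
2. **Data processing and analysis:** include MEP status as a factor and time since stroke as a covariate in the FMA-UE model. The covariate is needed because stratifying on MEP does not balance time since stroke.
3. **Discussion and conclusions:** limit the main conclusion to stroke 1 week to 6 months after onset with FMA-UE ≤ 26. Label any statement on severe tract damage as exploratory, drawn from the MEP-absent stratum, and do not extend the conclusion to chronic stroke.

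Stratification alone does not turn the sample into the hypothesised population, because entry is unchanged. The third step resolves the mismatch; the first two protect precision and make the exploratory look orderly.

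**Cost.** MEP is already measured before treatment, but it must now be done before the envelope is opened. There are two lists instead of one, arms may depart slightly from 12, one or two degrees of freedom are spent, and the conclusion is narrower.

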#### Exclusion criteria

The following are the exclusion criteria: (1) severe functional impairment: significant cognitive impairment (MMSE < 24), visual field impairment, hearing impairment or aphasia (confirmed by Boston Diagnostic Aphasia Test); (2) contraindications of rTMS: acute craniocerebral trauma or cerebral hemorrhage, history of epilepsy or epileptiform discharge detected in EEG; (3) unstable general condition: uncontrolled hypertension (SBP > 180 mmHg), severe heart, liver and kidney failure (NYHA grade III-IV), active malignant tumor; (4) motor system complications: modified Ashworth spasticity scale score ≥ 3 or rest tremor (UPDRS-III tremor item ≥ 2 points); (5) MRI/TMS contraindications: implantation of electronic devices (cardiac pacemakers, drug pumps, etc.), non-titanium alloy intracranial aneurysm clips, skull metal implants; (6) unable to cooperate with the examination: claustrophobia (clinical diagnosis) or fMRI tolerance failure caused by movement disorder; (7) pregnant or lactating women (negative urine pregnancy test before enrollment in women of childbearing age).

